## Abstract

**Introduction::**

Although automobile driving is often necessary in daily life, most package inserts for psychotropic drugs in Japan prohibit patients from driving under the influence of medication. This may be partially because no system to evaluate the influence of drugs on driving performance has been established. Standardized evaluation methods have been established in the Netherlands and the United States, but these cannot be implemented in Japan because of differences in road situations, traffic laws, and ethnicities. Therefore, to establish a method to evaluate the influence of drugs on driving performance in Japan, we planned a validation study using alcohol and a driving simulator (DS) and set a clinically meaningful threshold involving the standard deviation of lateral position (SDLP), which is a criterion standard evaluation item.

**Methods::**

This study was designed as a double-blind, placebo-controlled, randomized, 4-way, fourth-order crossover trial (Williams design). Twenty-four healthy Japanese men aged 21 to 64 years will be recruited through advertisements. The participants will be required to drive daily for over 3 years and to carry the active-type aldehyde dehydrogenase (ALDH) gene polymorphism (ALDH 2∗1/∗1). Participants will be randomly assigned to 4 groups based on blood alcohol concentration (BAC): 0% (placebo), 0.025%, 0.05%, and 0.09%. The amount of alcohol intake will be calculated based on Widmark formula using a beverage that is a mixture of 40% vodka and orange juice. After a practice period, each examination period will be set with 6-day intervals. The primary outcome is SDLP in a 60-minute road-tracking test using the DS. The secondary outcomes are other evaluation items in the DS tasks and DS sickness and sleepiness according to questionnaire responses. The estimated difference in SDLP between BAC levels of 0.05% and 0% will be calculated using a linear model.

**Ethics and dissemination::**

Ethics approval was obtained from the Ethics Committee at Hakata Clinic and the Nagoya University Medical School Hospital Bioethics Review Committee. The trial results will be disseminated through peer-reviewed publications and international conferences.

**Trial registration::**

This study was registered at ClinicalTrials.gov NCT 03572985 on June 28, 2018.

## Introduction

1

Automobile driving is an important means of transportation in modern society and an indispensable everyday activity for many people who live outside of large cities where no well-organized public transportation is available. This is also true for patients with mental disorders that require continuous medication to improve symptoms and prevent relapse. However, the World Health Organization has published a policy brief for drug use and road safety indicating that the effects of prescription drugs could not be underestimated.^[1]^ In addition, the US Food and Drug Administration has asked pharmaceutical companies to examine the influence of drugs that affect the central nervous system on driving.^[2]^ In Japan, although conclusive evidence is lacking, almost all the package inserts for psychotropic drugs prohibit patients from driving under the influence of medication. These uniform regulations restrict patients’ daily lives.

One of the reasons for this situation is that no system has been established in Japan for evaluating the influence of drugs on driving performance. Despite considerable research on driving performance in many countries, each research facility uses different evaluation methods, such as actual vehicle tests and driving simulators (DSs).^[3]^ Recently, results regarding the effect of sleeping pills on driving performance have been considered in devising recommended clinical dosages^[4]^; however, only the evaluation system in the Netherlands using actual cars^[5]^ and that in the United States using DSs^[6]^ is used in drug approval applications. In particular, the evaluation of vehicle “weaving” in the lateral direction became an index of driving performance referred to as the standard deviation of lateral position (SDLP), and currently, this remains the only fully validated index.^[3]^ Although these evaluation systems are accepted as standard methods abroad, the traffic laws and road conditions in foreign countries differ considerably from those in Japan. Moreover, the results obtained by those evaluation systems can be affected by ethnic differences, especially the evaluation system in the Netherlands, which has been verified only on long-distance linear expressways; therefore, using the same evaluation methods across countries and cultures is difficult. The establishment of a system in Japan that evaluates the influence of drugs on driving performance could provide useful information for Japanese patients and physicians.

Therefore, with the aim of establishing such an evaluation system, we planned a validation study using a DS and alcohol that would meet legal standards around the world. The purpose of this study targeting healthy adult males is to set a clinically meaningful SDLP threshold as a main evaluation item based on the difference between SDLP at blood alcohol concentration (BAC) levels of 0.00% and 0.05%. We set the SDLP threshold with a BAC of 0.05% as the impaired level. The upper limit of BAC set by law ranges from 0% to 0.08% from country to country.^[7]^ However, the International Council on Alcohol, Drugs, and Traffic Safety^[8]^ reported a BAC <0.05% is relatively safe, a BAC of 0.05% to 0.08% induces mild to moderate side effects, and a BAC of ≥0.08% poses a potentially dangerous risk. In fact, in most countries, a BAC of 0.05% is set as the upper limit. Although some reports have shown that cooperative muscle movement is impaired starting at a BAC of 0.035%,^[9]^ epidemiological studies have indicated that the risk of being involved in a traffic accident increases only slightly at BAC levels of ≤0.04%,^[10]^ increases by about double around a BAC level of 0.05%, and increases exponentially starting at a BAC level of 0.10%.^[11]^ Therefore, for the purposes of this study, we decided to use a BAC level of 0.05% as a threshold for clinically meaningful driving impairment. As a BAC level of ≥0.10% can easily cause drunkenness, 4 BAC levels (0.00% [placebo], 0.025%, 0.05%, and 0.09%) will be set to calculate the SDLP regression curve. The hypothesis of this study is that SDLP will increase in accordance with BAC levels.

## Methods

2

### Study design

2.1

This study was designed as a double-blind, placebo-controlled, randomized, 4-way, fourth-order crossover trial (Williams design). It will be an intervention study (alcohol intake and DS operation) with no drug administration. Taisho Pharmaceutical Co., Ltd., will be conducting the clinical trial at Fukuoka Mirai Hospital in Japan. To allow the participants to become accustomed to operating the DS, a practice period involving the same contents as the examination period will be established. The practice period will be conducted during a 2-day/1-night hospitalization stay and the examination period during a 3-day/2-night stay. A 6-day interval period will be implemented between the practice and examination periods.

### Participants

2.2

Healthy Japanese men were recruited through online advertisements and from Fukuoka Mirai Hospital. Because this is an exploratory study, the sample size was set to 24 participants in reference to the sample size of previous studies conducted to confirm the validity of a DS.^[6,12]^ The inclusion criteria are: age between 21 and 65 years; body mass index between 18.5 and 24.9 kg/m^2^; active-type aldehyde dehydrogenase (ALDH) gene polymorphism (ALDH 2∗1/∗1); alcohol consumption >2 days a month; able to drink a prespecified amount of alcohol in 30 minutes; possession of a driver's license and driving daily for >3 years; consistent sleeping pattern (wake up between 06:00 and 09:00 am, go to bed between 21:00 and 00:00 pm); no visual impairments; able to operate a DS with a full understanding of all DS tasks; judged by a physician as being able to participate; and able to provide written informed consent before the examination begins. The exclusion criteria are: having a disease recognized as being nonhealthy by a physician; a history of drug or food allergies; 3) serious allergic predispositions; 4) a history of stroke, head trauma, epilepsy, or malignant tumor; more than a 3-month history of sleep disorders, a medical history of sleep apnea syndrome or restless legs syndrome, or a history of hypersomnia such as narcolepsy; use of over-the-counter drugs within 1 week after starting the practice period; use of sedative hypnotics within 4 weeks after starting the practice period; experiencing more than a 6-hour time difference within 4 weeks after starting the practice period; irregular shift work and night shift work within 4 weeks after starting the practice period; experience using the same DS evaluation method as that used in the present study; a daily routine of alcohol consumption until sleep; unable to stop drinking from 2 days before until the day of the screening test, and from 2 days before hospitalization until discharge; smoking during hospitalization; donating blood within 12 weeks; use of prescription drugs within 4 weeks after starting the practice period; a diagnosis or history of alcoholism or drug dependency; positive result from a urine drug test during screening; unable or unwilling to comply with the study protocol; and judged unsuitable for participation by a physician. The discontinuance criteria are: noncompliance with the study protocol; experiencing adverse events that compel a physician or the participant himself/herself to cease participation in the trial; the participant chooses to discontinue the trial of their own volition; sliding off the track or have a large SDLP such as >60 cm during the practice period; and judged unsuitable for participation by a physician.

### Randomization and blinding

2.3

In total, 24 registered participants will be assigned to the following 4 sequences based on BAC: 0%, 0.025%, 0.05%, and 0.09%. The participants will be assigned randomly so that the ratio of each sequence will be 1:1:1:1 (Table 1). Randomization will be conducted based on a computer-generated random number table, with allocation conducted by an assignment manager uninvolved in data collection and not disclosed until the BAC groups are fixed. Therefore, the participants and investigators will be blinded to the allocation. However, in addition to the assignment manager, the allocations are planned to be disclosed to the institution for BAC measurement.

**Table 1 T1:**
[figure not shown]
Allocation of the participants into groups based on BAC.

### Determination of alcohol intake

2.4

In previous studies, the amount of alcohol intake has been calculated individually based on body water content.^[12,13]^ Therefore, we decided to calculate the amount of alcohol intake based on Widmark formula using a beverage that is a mixture of 40% vodka and orange juice. Using this formula, tests are conducted in the morning and afternoon, so the following equation will be used: 

The variables used in Widmark formula are defined in Table 2.

**Table 2 T2:**

Definition of variables used in Widmark formula.

The average of the BAC measured before and after the DS evaluation will be taken as the BAC at the DS evaluation.

BAC calculation formula in the morning: X = (Cm × 10 + 0.15) × W × 2.44 (mL)BAC calculation formula in the afternoon: X = (Cm × 10 + 0.089) × W × 2.44 (mL)

### ALDH2 genotype test

2.5

In this study, the ALDH2 genotype test will be performed by blood sampling at the screening stage. Although previous studies conducted outside of Japan have carried out DS validation using alcohol,^[14]^ generally, Asians, including Japanese, cannot drink as much alcohol as Europeans and North Americans; therefore, careful attention is needed in experimental designs targeting Japanese populations. Almost 100% of Caucasoids have the *ALDH2 ∗ 1* gene, which is associated with enhanced alcohol metabolism,^[15]^ whereas about 10% to 60% of Mongoloids have the *ALDH 2 ∗ 2* gene, which is associated with low enzyme activity.^[16]^ In the case of *ALDH 2 ∗ 2*, the accumulation of aldehydes may affect the results, making them difficult to compare with those of previous studies. Therefore, to check whether the participants had the *ALDH 2 ∗ 1* gene, all patients will undergo a blood sampling test before the DS task.

### Experimental schedule

2.6

A flowchart of the experiment is shown in Figure 1. The examination is divided into a screening period, a practice period, and 4 test periods. The interval between the practice period and test period 1 is 7 days, and the interval between each test period is 6 days. All participants will undergo screening tests, including assessment of background characteristics, a medical examination, check of vital signs, electrocardiogram, hematological examination, urine drug test, ophthalmic examination, and genetic test for ALDH2 during the screening period. The medical examinations and vital sign checks will be conducted at the time of hospital admission (Days 1, 8, 16, 24, and 32) and discharge (Days 1, 10, 18, 26, and 34) and before the DS task (Days 1, 9, 17, 25, and 33) during the practice and test periods. The time schedule of the test period is shown in Table 3. Participants will be given a chance to become accustomed with operating the DS on the evening of the first day of admission (days 1, 9, 17, 25, and 33) during the practice and test periods. They will be admitted to the hospital the day before the DS task and subjected to DS experiments the day after admission; all participants will be discharged from the hospital at 3 days after admission after their safety has been confirmed. All participants will also be evaluated using the Simulator Sickness Questionnaire (SSQ) before and after the DS task on Day 1, the Karolinska Sleepiness Scale (KSS), and the Profile of Mood States (POMS) 2 before the DS task on days 1, 9, 17, 25, and 33. Blood sampling for BAC measurements will be conducted before and after the DS task on Days 9, 17, 25, and 33.

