### Other outcomes

2.10

In addition to the DS evaluation, the following items will also be evaluated. Considering the possibilities of DS sickness and drowsiness at the time of the examination and alcohol-induced mood changes affecting the results, the Japanese version of the KSS,^[20]^ Japanese version of the POMS 2,^[21]^ and SSQ^[22]^ will be conducted simultaneously.

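### As printed, the Simulator Sickness Questionnaire is given only on the practice day, so simulator sickness, a named outcome, has no data at any assigned BAC level

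*Protocol article*

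**What the plan says.** All references are to the protocol article.

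- **SSQ timing (Section 2.6).** Participants are "evaluated using the Simulator Sickness Questionnaire (SSQ) before and after the DS task on Day 1".
- **Sleepiness and mood timing (same sentence).** The Karolinska Sleepiness Scale (KSS) is listed together with the "Profile of Mood States (POMS) 2 before the DS task on days 1, 9, 17, 25, and 33".
- **Period structure (Section 2.6).** "The examination is divided into a screening period, a practice period, and 4 test periods".
- **Blood alcohol sampling (Section 2.6).** "Blood sampling for BAC measurements will be conducted before and after the DS task on Days 9, 17, 25, and 33".
- **Outcome status.** The abstract counts "DS sickness and sleepiness according to questionnaire responses" among the secondary outcomes. Section 2.9, which lists the secondary outcomes, contains only simulator measures. The questionnaires appear in Section 2.10 under other outcomes.
- **Purpose (Section 2.10).** The questionnaires are included "Considering the possibilities of DS sickness and drowsiness at the time of the examination and alcohol-induced mood changes affecting the results", and the section says they are carried out at the same time as the simulator evaluation.
- **Analysis (Section 2.11).** Basic statistics are planned for the secondary outcomes. No comparison of questionnaire scores across BAC levels is described.

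**The concern.** Section 2.6 does not merely leave out the test-day SSQ. It gives the SSQ its own timing, Day 1, in the same sentence that gives a five-day list for the mood scale. Read literally, this is a deliberate difference. It puts the only sickness measurement in the one driving period that has no randomised condition.

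Two things are at stake. First, an outcome named in the abstract would have no data under placebo or any alcohol level, so even a simple table of sickness by BAC level could not be filled. Second, the check that Section 2.10 describes, whether sickness during testing may have influenced the driving results, could not be made for the drives that produce those results.

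The difference in labels adds a practical point. Section 2.11 states a summary for secondary outcomes, so whether that summary covers the questionnaires depends on whether the abstract or Section 2.10 is followed.

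**Working it through.** The plan states no figure to reproduce here. The check compares the assessment days with the test days and counts the overlap.

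**Inputs**

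- Participants: 24 (Sections 2.2 and 2.3).
- Assigned conditions: four BAC levels, 0%, 0.025%, 0.05% and 0.09% (Section 2.3), one per test period in a four-way crossover.
- SSQ days: {1} (Section 2.6).
- KSS and POMS 2 days, on the likelier reading of the sentence: {1, 9, 17, 25, 33} (Section 2.6).
- Days with blood alcohol sampling: {9, 17, 25, 33} (Section 2.6).

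**Step 1: which day is practice.** Section 2.6 has one practice period followed by four test periods, and five driving days: 1, 9, 17, 25 and 33. Blood alcohol is sampled on the last four only. Day 1 is therefore the practice day and Days 9, 17, 25 and 33 are the test days. Section 2.1 says the practice period has the same contents as the examination period. Even so, the four assigned levels fill the four test periods, so Day 1 carries no randomised level.

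**Step 2: overlap for the SSQ.** {1} and {9, 17, 25, 33} have no day in common.

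- Conditions with an SSQ score: 0 of 4.
- Participant-periods planned: 24 x 4 = 96.
- Participant-periods with an SSQ score: 0 of 96.

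**Step 3: overlap for KSS and POMS 2.** {1, 9, 17, 25, 33} contains all four test days.

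- Conditions with a score: 4 of 4.
- Participant-periods with a score: up to 96 of 96, each taken before driving.

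**Step 4: side by side**

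| Instrument | Practice day | Test days | Status in abstract | Status in Sections 2.9 and 2.10 |
|---|---|---|---|---|
| SSQ (sickness) | before and after | none | secondary | other |
| KSS (sleepiness) | before | before, all four | secondary | other |
| POMS 2 (mood) | before | before, all four | not named | other |

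Only the SSQ row conflicts with the purpose in Section 2.10. The status columns disagree for both sickness and sleepiness.

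**The case against.** **It may be a drafting slip.** The detailed time schedule (Table 3) and the flowchart (Figure 1) are not visible in the text reviewed, and Table 3 is a natural place for test-day questionnaires. The sentence in Section 2.6 is awkward, and other day lists there disagree. Admission is on Days 8, 16, 24 and 32, but the familiarisation session on the first evening of admission is put on Days 9, 17, 25 and 33. This stands as a caution: nobody can say from the article that sickness will in fact go unmeasured. It does not remove the point. If Table 3 has the SSQ on test days, the timing in Section 2.6 is wrong as printed.

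**The word examination could include practice.** Section 2.6 uses it for the whole sequence, practice period included, so a Day 1 SSQ might be said to satisfy Section 2.10. But Section 2.1 separates the practice period from the examination period, and the results that Section 2.10 wants to protect come from the test drives.

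**The secondary label rests on the abstract alone.** This is correct, and it is why the labels need to be aligned. The purpose stated in Section 2.10 conflicts with the schedule whichever label is used.

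**Stronger readings that the document does not support**

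- *Sleepiness cannot be compared across BAC levels either.* It can. The KSS is given in every test period, so each participant has one score per level. Whether it follows drinking is not stated in Section 2.6 and cannot be judged without Table 3.
- *The absence of a KSS after the drive is an error.* Nothing in the article promises a measure of drowsiness building up over the 60 minutes. A further KSS would be an optional improvement.
- *A planned comparison of questionnaires across BAC levels is lost.* The article states no formal comparison, only a supporting purpose and basic statistics.
- *The SDLP result becomes uninterpretable.* The aim is the total SDLP difference between BAC 0.05% and 0% in a randomised, placebo-controlled crossover. Sickness caused by alcohol would be part of that effect, and sickness caused by the simulator itself is expected under placebo too. The primary contrast does not need the SSQ.

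**Conclusion.** The point holds for the SSQ. As Section 2.6 is printed, simulator sickness is measured in 0 of 4 BAC conditions and 0 of 96 planned participant-periods. This contradicts its listing as a secondary outcome in the abstract and its purpose in Section 2.10. It is a stated timing that defeats its own outcome, not a detail left to a fuller document.

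The count assumes that Section 2.6 is followed literally. Table 3 could show otherwise, in which case the fault is in the wording of Section 2.6 and not in the conduct. The passages need reconciling either way.

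The scope is limited. The sleepiness and mood data can be used at every BAC level, and the primary SDLP analysis is unaffected. What is lost is one supporting outcome and the check on sickness that Section 2.10 describes. The change is worth making, but the trial's main conclusion does not depend on it.

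**What to change.** Choose one of the following and make the text consistent with it.

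1. **Keep sickness as an outcome.** In Section 2.6, schedule the SSQ before and after the simulator task on Days 9, 17, 25 and 33 as well as Day 1, and summarise the scores and the change from before to after by BAC level. If Table 3 already has this schedule, only the sentence in Section 2.6 needs correcting.
2. **Drop sickness as an outcome.** State that the SSQ is a practice-period check only, remove sickness from the outcomes in the abstract, and amend the rationale in Section 2.10.

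Under either option, make the abstract and Sections 2.9 and 2.10 agree on whether the retained questionnaire measures are secondary or other outcomes, so that it is clear whether the summary in Section 2.11 covers them.

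Option 1 adds two short forms per test day, 96 x 2 = 192 across the trial. That is a few minutes of self-report per test day with an instrument already in use, plus a schedule amendment. Option 2 costs only an edit, but gives up the sickness check. A KSS after the 60-minute drive could be added at the same time if wanted; it is not needed to resolve the inconsistency.

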**Figure 1 F1:**
[figure not shown]
Flowchart of the experiment. DS = driving simulator.

**Table 3 T3:**
[figure not shown]
Time schedule of the test period.

### DS task

2.7

The DS software runs on a PC (Windows 10) equipped with a steering wheel, brake pedal, and accelerator system (Driving Force GT, Logicool). The image from the PC is projected on an 80-inch screen using a liquid crystal projector (EB-X05, Epson, Nagano, Japan). The DS tasks consist of the following. In a road-tracking test, the participants are instructed to drive in the center of the left lane while maintaining a speed of 100 km/h on a 2-lane road with gentle curves. The SDLP, which indicates weaving, is used as a performance measure. The measurement time is 60 minutes from 9:00 or 10:15 on the DS evaluation day. In a car following test, the participants are instructed to maintain a constant intervehicle distance from a preceding vehicle with varying speeds. When the preceding car decelerates, its brake lights come on. Performance is measured as the coefficient of variation (CV), which is obtained by dividing the standard deviation of the distance between the cars by the mean value. Therefore, a smaller CV of the distance to the preceding vehicle (DCV) indicates better performance. The measurement time is 5 minutes from 15:00 or 16:15 on the DS evaluation day. In a harsh braking test, the participants are instructed to maintain a constant speed of 50 km/h and to avoid colliding with humanoid models randomly appearing from either side of the road by harsh braking. This test consists of seven harsh braking trials over a 5-min period, and is conducted continuously after the completion of the car following task. The DS tasks are conducted in a dark, sound-attenuated room and based on our previous DS tasks.^[17]^ Driving performance is recorded every 20 ms.

